| Pregnancy loss            | All cases of pregnancy loss follow-                                            | Yes/no | Registration in medical records or detection of empty | Assessed continuously in patients with a positive pregnancy                                                                                              |

|                                     |                                                                                                  |        |                                                                                                              |                                                                                                                                                          |
|-------------------------------------|--------------------------------------------------------------------------------------------------|--------|--------------------------------------------------------------------------------------------------------------|----------------------------------------------------------------------------------------------------------------------------------------------------------|
|                                     | ing a positive pregnancy test, before GA 22+0                                                    |        | uterus/fetal demise at early pregnancy scan                                                                  | test, depending on the time point of pregnancy loss                                                                                                      |
| Ectopic pregnancy                   | Pregnancy detected outside of the uterus, using either a) ultrasound or b) histologic testing    | Yes/no | Registration in medical records or detection of ectopic pregnancy during the early pregnancy ultrasound scan | Assessed continuously in all patients with a positive pregnancy test                                                                                     |
| Induced abortion                    | Medically or surgically induced abortion, typically due to congenital abnormality in fetus/child | Yes/no | Registration in medical records                                                                              | Assessed continuously in all patients with a positive pregnancy test                                                                                     |

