| Gesta-
tional
diabe-
tes | Diabetes detected during pregnancy with oral glucose tolerance test. | Yes/no | Registration in medical records |                                                                                                                                                          |
| Post-
partum
bleed-
ing  | Bleeding exceeding 1000 mL                                           | Yes/no | Registration in medical records |                                                                                                                                                          |
| Caesar-
ean sec-
tion       |                                                                      | Yes/no | Registration in medical records |                                                                                                                                                          |
| Perinatal complications    |                                                                      |        |                                 | Approximately one year after inclusion in trial (one-year follow-up) for all patients with a verified clinical pregnancy and no record of pregnancy loss |
| Preterm birth                     | Birth before GA 37+0                                                 | Yes/no | Registration in medical records |                                                                                                                                                          |
| Birth-
weight                  |                                                                      | Grams  | Registration in medical records |                                                                                                                                                          |
| Low birth weight                  | Birthweight < 2500 grams                                             | Yes/no | Registration in medical records |                                                                                                                                                          |
| Very low birth weight             | Birthweight < 1500 grams                                             | Yes/no | Registration in medical records |                                                                                                                                                          |

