| Hight birth weight                | Birthweight > 4000 grams                                             | Yes/no | Registration in medical records |                                                                                                                                                          |
| Very high birth weight            | Birthweight > 4500 grams                                             | Yes/no | Registration in medical records |                                                                                                                                                          |

|                           |                                                                                                |        |                                                      |  |
|---------------------------|------------------------------------------------------------------------------------------------|--------|------------------------------------------------------|--|
| Small for gestational age | More than two standard deviation units below expected birth weight.                            | Yes/no | Calculated following collection of birth-weight data |  |
| Large for gestational age | More than two standard deviation units above expected birth weight.                            | Yes/no | Calculated following collection of birth-weight data |  |
| Congenital malformation   | Any congenital malformation                                                                    | Yes/no | Registration in medical records                      |  |
| Perinatal death           | Stillbirth or live birth followed by death within the first week following birth, from GA 22+0 | Yes/no | Registration in medical records                      |  |

GA = gestational age, hCG = human chorionic gonadotropin

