### 26c. Calculations or transformations applied to outcomes.

In the final analysis the rate of the above outcomes will be calculated using the formula:  $n \text{ events} / N \text{ individuals in study group}$  in a given study population supplied by percentages.

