### **30. Harms**

Progesterone is routinely used for patients undergoing ovarian stimulation and embryo transfer and is not expected to cause harm to participants. The timing of embryo transfer will not cause any harm to the patients. Apart from extra study visits and blood samples, this study will cause very modest harm to participants.

In case of adverse reactions (AR), serious adverse events (SAEs), serious adverse reactions (SARs) and suspected unexpected serious adverse reactions (SUSARs) these will be registered

by allocated study staff according to study protocol. Data on patient safety and potential SAEs, SARs and SUSARs will be reported to the Danish Medicines agency annually according to Danish law.

Should patients participating in the trial give birth to children with congenital malformations or in the rare event of perinatal death, these outcomes will be publicly disseminated under “perinatal outcomes”, including comparisons of these outcomes across study groups.

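### Malformations that end in induced abortion have no stated route into the SAP's congenital malformation count

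*SAP*

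**What the plan says.** The outcome table in SAP section 26a-b lists congenital malformation among the perinatal complications and defines it as "Any congenital malformation", taken from medical records. The time and population given for that block are "Approximately one year after inclusion in trial (one-year follow-up) for all patients with a verified clinical pregnancy and no record of pregnancy loss". Section 15 repeats the rule for obstetric and perinatal outcomes.

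Induced abortion is a separate yes/no outcome in the same table: "Medically or surgically induced abortion, typically due to congenital abnormality in fetus/child". It is "Assessed continuously in all patients with a positive pregnancy test". The row asks for no indication and gives no gestational limit. Pregnancy loss covers all losses after a positive test and before GA 22+0. Rows for ectopic pregnancy, induced abortion, and early and late miscarriage follow it.

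Section 30 addresses malformations in these terms: "Should patients participating in the trial give birth to children with congenital malformations". Together with perinatal death, they are to be published under perinatal outcomes, "including comparisons of these outcomes across study groups". Under section 26c every rate is the number of events divided by the individuals in the study group.

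**The concern.** The outcome is labelled as covering any malformation, yet its follow-up population is defined by the absence of a recorded pregnancy loss. The SAP itself names congenital abnormality as the typical reason for induced abortion. It therefore recognises a group of affected pregnancies and gives no rule for bringing them into the malformation outcome. Two analysts with the same records could report different counts.

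This matters because section 30 promises a comparison of malformations across the randomised groups. A count that depends on whether the pregnancy was ended depends on something that happens after randomisation. Because the section 26c denominator is everyone in the group, an omitted case lowers that group's rate and nothing in the denominator shows that a case is missing.

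**Working it through.** **Reading the text**

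The outcome of a pregnancy with a malformation, ended by induced abortion before GA 22+0, turns on one unstated point.

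- *Induced abortion is a pregnancy loss.* The woman has a record of loss and falls outside the one-year follow-up (sections 15 and 26a-b). Her case appears as an induced abortion, without a reason, and not as a malformation.
- *Induced abortion is not a pregnancy loss.* She stays in follow-up and the section 26 definition can include her case. Section 30 still speaks only of children born, so the two sections differ in scope.

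Table order favours the first reading, since induced abortion sits between ectopic pregnancy and the miscarriage rows, after the pregnancy loss row. No sentence says so, and indentation may have been lost when the PDF was read.

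**The plan's own figure**

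The SAP gives no figure for malformations. Its only relevant figure is the total of 604 women in section 11. For 21% against 31%, two-sided 5%, 80% power, pooled variance:

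n = [1.96 × √(2 × 0.26 × 0.74) + 0.8416 × √(0.21 × 0.79 + 0.31 × 0.69)]² / 0.10² ≈ 301 per side, or 602.

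This agrees with 604. It does not bear on the point beyond giving 604 / 2 = 302 women on each side of each comparison.

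**Size under assumed rates**

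Let m be the share malformed among births plus terminated malformed pregnancies, and t the share of malformed pregnancies that are terminated. Both are assumptions: m from 2% to 4%, t from 10% to 50%. Births per side are 302 times the live birth rate in section 11.

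- All malformations = births / (1 − m·t) × m
- Counted = all × (1 − t)
- Missed = all × t

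| Live birth rate | m | t | Births | All | Counted | Missed |
|---|---|---|---|---|---|---|
| 21% | 2% | 10% | 63.4 | 1.27 | 1.14 | 0.13 |
| 21% | 2% | 50% | 63.4 | 1.28 | 0.64 | 0.64 |
| 31% | 4% | 10% | 93.6 | 3.76 | 3.38 | 0.38 |
| 31% | 4% | 30% | 93.6 | 3.79 | 2.65 | 1.14 |
| 31% | 4% | 50% | 93.6 | 3.82 | 1.91 | 1.91 |

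Over the whole range, about 0.1 to 1.9 cases per side are missed. With N fixed at 302, the rate falls by the fraction t: in the fourth row, 2.65/302 = 0.88% counted against 3.79/302 = 1.26% in all.

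**Effect on the contrast**

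Take an assumed 3 true cases against 2 (difference 1, ratio 1.5) and apply different terminated shares.

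| t, first group | t, second group | Counted | Difference | Ratio |
|---|---|---|---|---|
| 30% | 30% | 2.1 v 1.4 | 0.7 | 1.50 |
| 30% | 10% | 2.1 v 1.8 | 0.3 | 1.17 |
| 10% | 30% | 2.7 v 1.4 | 1.3 | 1.93 |
| 50% | 10% | 1.5 v 1.8 | −0.3 | 0.83 |

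Equal shares shrink the difference and leave the ratio unchanged. Unequal shares can weaken the contrast, strengthen it or reverse it.

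**The case against.** The strongest reply is that nothing is lost from the report. Induced abortion is an outcome in its own right, assessed in all women with a positive test, under the same rate formula and the same tests of proportions. An excess in one group would show in that row. A reader might infer that these pregnancies are never counted; the SAP does not support that. They are counted, but under a heading that does not identify them as malformations and without a reason. This part of the reply stands.

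It is also fair that the exclusion rests on reading induced abortion as pregnancy loss, which the SAP does not state, and that an abortion at or after GA 22+0 lies outside its definition of loss. Section 30 promises publication if affected children are born and does not expressly rule out other cases. The SAP writes of abnormality in one row and malformation in another and does not equate them. These points turn a certain exclusion into an ambiguity, but they do not remove it, because neither reading gives a consistent rule across sections 26 and 30.

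Reporting malformations among births, with induced abortion as a separate row, would be coherent if the SAP said that this is what it means. The label and the definition say otherwise.

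Finally, the numbers are small. Adding two missed cases to one side would turn 2 v 2 into 4 v 2 of 302 each, with a Fisher exact p of about 0.69. No powered conclusion changes. That limits the weight of the point but does not argue against defining the outcome.

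**Conclusion.** The point holds as a gap in ascertainment. The SAP promises a between-group comparison of malformations and does not fix whether cases ended by induced abortion belong in it. If they are left out, each group's rate is too low by its share terminated, and the contrast is distorted in an unknown direction when those shares differ.

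Two stronger inferences are not supported. One is that the comparison itself is necessarily too low: only the absolute rates are, and with equal shares the ratio is unaffected. The other is that malformation is the only fetal safety outcome compared. Section 30 makes the same promise for perinatal death, and section 26 lists several other perinatal outcomes.

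The size, roughly 0 to 2 cases per side, rests wholly on the assumed 2-4% and 10-50%, since the SAP gives neither. The primary outcome and the sample size are untouched. The change is worth making because it is cheap and the count is small enough for one or two cases to alter the safety table.

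**What to change.** - In section 26a-b, state whether an induced abortion is a record of pregnancy loss.
- Extract the indication for each induced abortion from the medical records already used for that outcome.
- Assess malformation in all women with a verified clinical pregnancy. Report per group the total over births plus terminations or losses with a recorded malformation, and show the number at birth separately. The section 26c denominator can stay.
- Reword section 30 to the same scope.

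The cost is SAP wording, one extra extraction field and a slightly higher reported malformation count. Showing births separately keeps the births-only figure available.

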### 26c. Calculations or transformations applied to outcomes.

In the final analysis the rate of the above outcomes will be calculated using the formula:  $n \text{ events} / N \text{ individuals in study group}$  in a given study population supplied by percentages.

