## 20. Analysis Populations

Per-transfer (primary population): Women randomised, undergoing embryo transfer

Intention-to-treat: Women randomised.

As-treated: Women randomised, grouped according to treatment received.

Per-protocol: Women randomised, undergoing allocated treatment.

Women withdrawing consent to participate in the trial will be removed from all analyses.

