### **28. Missing Data**

For transparency, rates will be presented as a fraction (e.g. n events/n individuals in study group) and percentage.

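### One rate formula per woman for every listed outcome mixes complication risk with the live-birth effect; the denominator should be named for each outcome class

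*SAP*

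**What the plan says.** Section 26c follows directly on the outcome table and covers all of it: "In the final analysis the rate of the above outcomes will be calculated using the formula" of events over individuals in the study group, "in a given study population supplied by percentages". Section 28 gives the same fraction as its example: "rates will be presented as a fraction (e.g. n events/n individuals in study group) and percentage".

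Section 20 defines four populations: "Per-transfer (primary population): Women randomised, undergoing embryo transfer"; "Intention-to-treat: Women randomised"; and the as-treated and per-protocol sets. All four consist of randomised women. None is restricted to women with a positive test, an ongoing pregnancy or a birth.

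The table in section 26a-b includes outcomes that need a pregnancy or a birth, for example preterm birth, defined as "Birth before GA 37+0". It says that obstetric and perinatal outcomes are evaluated "for all patients with a verified clinical pregnancy and no record of pregnancy loss". That tells the reader who is assessed; it does not make that group the denominator.

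These outcomes are tested. Section 27a prescribes chi-squared tests and adjusted logistic regression for proportions. Section 27d substitutes Fisher's exact test for binary obstetric and perinatal outcomes when there are 10 events or fewer. Section 30 promises public reporting of malformations and perinatal deaths, "including comparisons of these outcomes across study groups".

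**The concern.** A woman who does not give birth cannot have a preterm birth. With all women in the denominator, she counts as a woman without the complication. An arm that produces more births then has more women exposed to the risk, and its per-woman complication rate rises even if each birth is exactly as safe as in the other arm. Conversely, an arm with fewer births looks safer.

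The outcomes concerned are hypertensive disorders, gestational diabetes, postpartum bleeding, caesarean section, preterm birth, the birth-weight categories, small and large for gestational age, congenital malformation and perinatal death. They are the trial's main evidence on maternal and child safety. Both interventions are meant to change the live birth rate, so the two effects are mixed in exactly the scenario the trial was designed to find.

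Pregnancy loss has a related but separate problem: its per-woman rate depends on how many women test positive.

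**Working it through.** **Inputs from the SAP.** Section 11: live birth 31% versus 21%, total 604, 80% power, 5% significance. Sections 9 and 12: allocation 1:1:1:1 with two pooled comparisons, so 302 women per side in each.

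**Input not in the SAP.** The risk of a complication per birth, *r*. No value is given, so a range of 5% to 30% is assumed, equal in both arms.

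**Step 1: reproduce the plan's figure.** Two-sided test with pooled variance and no continuity correction:

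n = [1.96·√(2·0.26·0.74) + 0.842·√(0.21·0.79 + 0.31·0.69)]² / 0.10² ≈ 301 per side, 602 in total.

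This agrees with 604 to within rounding. Power with 302 per side is 80.2%.

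**Step 2: expected births.** 302 × 0.31 ≈ 94 and 302 × 0.21 ≈ 63.

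**Step 3: the rate under section 26c.** Per-woman rate = P(birth) × *r*. With equal *r* the ratio is 0.31*r* / 0.21*r* = 1.48 whatever *r* is. The risk difference is 0.10 × *r*.

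| Assumed risk per birth | Per-woman rates | Difference (points) | Expected events per side |
|---|---|---|---|
| 5% | 1.55% vs 1.05% | 0.5 | 4.7 vs 3.2 |
| 8% | 2.5% vs 1.7% | 0.8 | 7.5 vs 5.1 |
| 10% | 3.1% vs 2.1% | 1.0 | 9.4 vs 6.3 |
| 20% | 6.2% vs 4.2% | 2.0 | 18.7 vs 12.7 |
| 30% | 9.3% vs 6.3% | 3.0 | 28.1 vs 19.0 |

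Live birth stands in here for birth and for ongoing pregnancy. For the obstetric outcomes the relevant ratio is that of ongoing pregnancies, for which the SAP gives no planning value.

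**Step 4: effect on the planned tests.** Simulation of 4,000 trials per value of *r*, with equal risk per birth and the SAP's own rule (Fisher at 10 events or fewer, otherwise chi-squared):

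| Risk per birth | p < 0.05, per woman | p < 0.05, per birth | More events in the arm with the higher live birth rate |
|---|---|---|---|
| 8% | 10% | 4.7% | 70% |
| 10% | 12% | 5.2% | 74% |
| 20% | 20% | 5.3% | 85% |
| 30% | 29% | 5.0% | 90% |

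With births as the denominator, the expected ratio is 1.00 and the rejection rate stays near 5%.

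**Step 5: pregnancy loss.** Its per-woman rate is P(positive test) × P(loss given a positive test). The live-birth ratio does not govern this product: an arm that gains births by preventing losses would show a lower per-woman loss rate. The 1.48 does not carry over.

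**The case against.** The strongest reply is that a per-woman rate is a legitimate estimand. It keeps the randomised comparison, whereas a per-birth rate conditions on an event after randomisation that both interventions aim to change. More preterm births per woman treated is a real consequence of an arm with more births. This stands. A reader might infer that the section 26c rate is wrong or the difference spurious; the SAP does not support that. The rate answers a different question from the one a complication rate answers.

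Second, the closing qualifier in section 26c, "in a given study population supplied by percentages", might be meant to allow a births-only group, and section 28 offers its fraction only as an example. Some ambiguity remains. But the SAP defines no such group, and limiting who is assessed does not set a denominator.

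Third, the size is modest for rare outcomes. At 8% risk per birth the expected counts are 7.5 versus 5.1. The standard error of the log ratio is √(1/7.49 + 1/5.07 − 2/302) = 0.57, so an approximate 95% interval around 1.48 runs from 0.5 to 4.5. A reader might infer that the better arm always looks worse; in the simulation at 8% it has more events in only 70% of trials. The larger rejection rates need assumed risks of 20% to 30%.

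Fourth, readers can partly rebuild conditional rates, because fractions are promised and live births are reported. That does not fix the denominator of the planned tests.

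A reader might also infer that the plan contradicts itself over birthweight in grams. It does not: section 26c governs rates, and a mean has no event count. Birthweight falls under the methods for continuous variables in section 27a.

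**Conclusion.** The point holds for the binary obstetric and perinatal outcomes. As section 26c is written, their comparison between groups combines complication risk with the live-birth effect. At the design effect and equal risk per birth, the expected ratio is 1.48, and the risk difference is 0.5 to 3.0 percentage points over an assumed risk per birth of 5% to 30%.

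The size rests on three assumptions: the true live birth rates equal the planning values, the risk per birth is the same in both arms, and live birth approximates ongoing pregnancy. If live birth does not differ between the arms, the mixing disappears from the comparison, although the percentages still cannot be read as complication rates.

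The primary outcome, its test and the sample size are untouched. This is an inexpensive improvement to how the secondary safety results can be read.

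**What to change.** In section 26c, name the denominator for each outcome class:

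- Live birth, clinical pregnancy and pregnancy: per woman in the analysis population, as now.
- Pregnancy loss and its types: per woman, and beside it per positive pregnancy test.
- Obstetric outcomes: per woman, and beside it per ongoing clinical pregnancy.
- Perinatal outcomes: per woman, and beside it per birth. The births counted should include stillbirths where the outcome does, as perinatal death does.

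Show the between-group comparison for both rates. Label the conditional ones as comparisons of post-randomisation subsets. Align the example fraction in section 28.

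The cost is a few lines of SAP text and one extra table column. No new data are needed, since pregnancy tests, scans and births are already recorded. The drawback is that randomisation does not protect the conditional comparisons, which is why the per-woman rate stays and the label is needed.
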